### Interim analyses {21b}

Not applicable. All data will be analyzed at the end of the experiment.

### Methods for additional analyses (e.g., subgroup analyses) {20b}

Not applicable. No additional analyses will be conducted.

### Methods in analysis to handle protocol non-adherence and any statistical methods to handle missing data {20c}

Missing data will be conducted by an intent to treat analysis (all randomized participants will be included with the last value carried forward), followed by a secondary “per-protocol” analysis (include only participants who followed all aspects of the protocol correctly).

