### Objectives {7}

#### Specific objectives

The aims of this study are to (1) compare the effects of monotherapy (either PL or tES) and combined therapy (PL + tES) on improving visual field function; (2) examine whether the interventions influence brain neural activity, and concentrations of neurotransmitters in the brain and blood; (3) investigate the degree to which enhancements in visual field or brain neural activity, brought about by the interventions, act as moderating factors in the improvement of mobility performance, mental health, fear of falling, and QoL; and (4) optimize the training protocol and the optimal dosage for achieving maximal intervention effect in glaucoma patients.

Hypotheses:The combination of PL and tES will result in greater visual field improvements than monotherapy.The intervention effect will increase with longer training duration.The improvement in the visual field induced by the interventions will be accompanied by changes in brain activities and blood biomarkers.An improved visual field will contribute to better balance function, gait performance, and QoL. It will also decrease fear of falling and symptoms of depression or anxiety in glaucoma patients.

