### Sample size {14}

The sample size calculation for linear multiple regression with three groups and six time points was performed using G*Power (version 3.1). According to the HRP results from phase 1 study [37] in the GREAT project (Cohen’s *f*^2^ = 0.1), a sample of 144 glaucoma patients will be needed to provide 80% power to detect a significant difference in visual field among three groups at the 2-tailed 0.05 alpha level, assuming a 20% dropout rate.

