## Statistical methods

### Statistical methods for primary and secondary outcomes {20a}

At the conclusion of this project, we will perform statistical analysis based on the intention-to-treat (ITT) principle. For the primary outcome, the differences of MD measured using the 24–2 SITA HFA will serve as an indicator of the effectiveness of interventions. Among the three groups, the intervention group showing the greatest improvement in MD will signify the strongest impact of rehabilitation. Additionally, changes in MD across six time points (baseline, interim 1, interim 2, post-intervention, 1-month post-intervention, and 2-month post-intervention) will reveal the dose-response relationship and recovery duration.

To address inter-individual variability, we will employ a linear mixed model with intervention type and time point as the fixed effect, and baseline MD value as the covariate. A dummy-coding scheme with the placebo PL + sham tES condition as the reference level will be utilized. Initially, a full model will be fitted, and if convergence issues or overfitting arise, adjustments will be made to the random intercept and slope. Model comparison will be conducted using a likelihood-ratio test to evaluate the adequacy of the current model relative to alternative models without the fixed effect. The level of statistical significance for analysis is set at a two-sided *p* < 0.05.

To address the potential attrition and missing data due to participant drop-out, we will conduct sensitivity analyses using multiple imputation methods. Specifically, we will employ the fully conditional specification (FCS) method. This method allows for the imputation of missing data for multiple variables with different distributions. By conducting these sensitivity analyses, we aim to assess the robustness of our primary analysis results to potential attrition bias and missing data. The multiple imputation approach will provide a principled way to handle missing data, ensuring that our conclusions are not unduly influenced by the potential non-random nature of missing data.

The analyses of secondary and exploratory outcomes will follow a similar approach to that of the primary outcome. A detailed statistical analysis plan for secondary and exploratory outcomes is being developed and will be reviewed of by the steering group prior to data analysis.

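### Section {20c} carries the last value forward in the ITT analysis, section {20a} specifies a mixed model with multiple imputation as sensitivity; the two are not reconciled, and carrying forward suits a growing effect badly

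*Protocol article*

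**What the plan says.** Two sections of the protocol article govern missing MD values.

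- **Statistical methods {20a}.** The article states that "we will perform statistical analysis based on the intention-to-treat (ITT) principle". For the primary outcome, "we will employ a linear mixed model with intervention type and time point as the fixed effect, and baseline MD value as the covariate". For attrition, "we will conduct sensitivity analyses using multiple imputation methods", and "we will employ the fully conditional specification (FCS) method". Changes in MD over the six visits "will reveal the dose-response relationship and recovery duration". LOCF does not appear.
- **Missing data and non-adherence {20c}.** Here the ITT analysis is the one in which "all randomized participants will be included with the last value carried forward", followed by a per-protocol analysis labelled secondary. Neither the mixed model nor imputation appears.

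Three other statements bear on the choice. The hypotheses include "The intervention effect will increase with longer training duration". The sample size was set "assuming a 20% dropout rate". The Discussion concedes that repeated testing may produce learning effects in every outcome and calls dropout a realistic concern.

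**The concern.** A linear mixed model uses each participant's observed visits and needs no filled-in values. A rule that fills every missing visit with the last observed value sets that feature aside and passes copies to the model as if they had been measured. For someone who leaves after baseline (T1), all five later values would equal the baseline MD, which is also the model's covariate.

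The rule also assumes that MD stops changing at dropout. That conflicts with the stated hypothesis of an effect growing over the three training blocks, and it blurs the time course from which dose-response and recovery duration are to be read.

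At stake is the primary estimate, because two analysts following different sections would report different numbers from the same data. Section {17b} unblinds only after data lock and gives the primary analysis to the unblinded statistician. If the conflict is left open, the choice could be made with allocation known.

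**Working it through.** **1. The plan's own figure.** The sample size section gives 144 for f² = 0.1, 80% power, two-sided 0.05 and 20% dropout. A noncentral F calculation with three tested predictors (a number inferred here, not stated) needs 114 participants. Then 114/0.8 = 142.5, which rounds up to 143, and the next multiple of three is 144. The 20% is therefore part of the plan, and it is the rate used below.

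**2. Assumptions the protocol does not supply.** T4, the visit at the end of training, is the comparison point. The difference between arms grows linearly, so the shares of the T4 difference reached at T1, T2, T3 and T4 are 0, 1/3, 2/3 and 1. Dropout is unrelated to outcome. The target is the difference had everyone continued.

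**3. Equal dropout.** With dropout d and mean share r reached at the last attended visit, LOCF retains (1 − d) + d·r of the T4 difference. At d = 0.2:

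- all leave after T1: 0.8 + 0.2 × 0 = 0.80
- all leave after T2: 0.8 + 0.2 × 1/3 = 0.87
- all leave after T3: 0.8 + 0.2 × 2/3 = 0.93
- spread evenly over the three: r = (0 + 1/3 + 2/3)/3 = 1/3, giving 0.87

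With even spread, d = 0.1 gives 0.9 + 0.1/3 = 0.93, and d = 0.3 gives 0.7 + 0.3/3 = 0.80.

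**4. Unequal dropout with a practice gain.** Assume a 1 dB practice gain in both arms, also linear to T4, and evenly spread leaving. The multipliers are then 0.933 at 10% dropout and 0.80 at 30%.

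- True difference 0, active 10% and placebo 30%: 0.933 − 0.80 = +0.13 dB. Reversed: −0.13 dB.
- True difference 1 dB, active 10% and placebo 30%: 0.933 × 2 − 0.80 = 1.07 dB. Reversed: 0.80 × 2 − 0.933 = 0.67 dB.

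**5. Follow-up.** Suppose the T6 effect is half the T4 effect and 20% leave after T4. LOCF shows 0.8 × 0.5 + 0.2 × 1 = 0.60 of the T4 effect instead of 0.50.

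**6. Simulation check.** 48 per arm, two arms, 400 runs; assumed between-person SD 4 dB and residual SD 1 dB. The comparator is a likelihood fit to the observed values, with a separate mean for each visit in each arm. Entries are mean T4 differences in dB.

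| Dropout active/placebo | True difference | Practice gain | Complete data | LOCF | Likelihood fit |
|---|---|---|---|---|---|
| 20%/20% | 1 | 0 | 1.00 | 0.86 | 0.99 |
| 20%/20% | 1 | 1 | 1.00 | 0.86 | 1.00 |
| 10%/30% | 1 | 1 | 0.99 | 1.06 | 0.99 |
| 30%/10% | 1 | 1 | 1.00 | 0.67 | 1.00 |
| 10%/30% | 0 | 1 | 0.01 | 0.15 | 0.02 |
| 30%/10% | 0 | 1 | 0.03 | −0.11 | 0.03 |

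The simulation agrees with the closed-form results within its random error.

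**The case against.** **The sections can be read together.** {20a} names a model and {20c} a rule for filling data, so LOCF-filled data could feed the mixed model, with imputation as the robustness check. That reading is possible, so it goes too far to say the article sets out two rival primary analyses. But no text states the combined reading, and it would discard the model's own handling of incomplete series.

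**A separate analysis plan may settle it.** {17b} mentions a pre-specified plan covering the primary analysis. However, {20a} describes only a plan for secondary and exploratory outcomes as in preparation, and the article itself states the primary analysis. The point is a conflict between two statements made, not a missing detail.

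**LOCF need not be biased.** This stands in part. The calculations target what leavers would have gained had they continued, and the article does not define its target that way. If leavers keep exactly what they had gained and gain no more, the evenly spread example has a true all-randomized difference of 0.87 dB. LOCF is then right, and the likelihood fit, at about 1.00, overstates it. A reader might infer that LOCF always biases the ITT result against the intervention; the documents do not support this.

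**Unequal dropout has no basis in the documents.** Also fair. The protocol gives one 20% figure, the arms have the same number of sessions, and participants are blinded. The 10% and 30% rates show only that the error has no fixed direction.

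**Two further inferences fail.** A reader might conclude that LOCF leaves nothing to impute. A sensitivity analysis would normally start from the original incomplete data, so this does not follow. A reader might also expect a large loss of power. The protocol gives no SD for MD, so the documents support no such figure.

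**Conclusion.** The concern holds as an unreconciled rule for the primary analysis, with LOCF the less suitable of the two statements given the trial's own hypothesis and its use of the visit pattern.

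The numerical effect is conditional. With linear growth to T4, and 20% dropout in each arm unrelated to outcome, LOCF understates the T4 difference by 7% to 20%, or 13% with evenly spread leaving. The understatement is smaller if stopping training stops the gain. With a shared 1 dB practice gain and 10% versus 30% dropout, a null difference shifts by about 0.13 dB in either direction. For dropouts after T4, a fading effect can look more durable than it is. Growth shape, dropout timing and balance, practice gain and later decay are all assumed; the Discussion says only that learning effects may occur.

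The conflict itself needs none of these assumptions and should be resolved before data lock.

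**What to change.** - In {20c}, delete LOCF or keep it only as a labelled sensitivity analysis.
- In {20a} and {20c}, name one primary ITT analysis: the linear mixed model fitted to all observed MD values of all randomized participants, without prior filling.
- Keep FCS multiple imputation as the sensitivity analysis and say that it includes participants with no post-baseline MD. With baseline MD only a covariate, they contribute nothing to the mixed model.
- Preferably add a delta-adjusted version of the imputation. {20a} is concerned with non-random missingness, whereas the mixed model and standard FCS both assume missing at random. It would also show how far the result depends on leavers gaining less than those who stay.
- Keep the per-protocol analysis as secondary.

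The cost is a few sentences in the protocol and analysis plan, plus some programming for the delta adjustment. No extra data or participants are needed.

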### Plans to give access to the full protocol, participant-level data, and statistical code {31c}

The datasets analyzed during the current study and statistical code are available from the corresponding author on reasonable request, as is the full protocol.

## Oversight and monitoring

### Composition of the coordinating center and trial steering committee {5d}

The coordinating center is School of Optometry, The Hong Kong Polytechnic University, and the project steering committee consists core research team members including [name], [name], [name], [name], and [name]. The monitoring committee and ethics committee are responsible for overseeing these procedures of this project. This includes the randomization of participants, ensuring the blindness of both participants and investigators, and maintaining the confidentiality of participants’ personal information.

### Composition of the data monitoring committee, its role and reporting structure {21a}

Not applicable. The intervention is non-invasive and has been proven safe.

### Adverse event reporting and harms {22}

Participants are closely monitored for any discomfort throughout the interventions and assessments. Investigators, who are also health care professionals and first aid qualified, will accompany and assist participants to ensure that they are not exposed to any hazards. If a research activity results in an injury, the laboratory is equipped with a first aid box and a telephone for emergency calls. Any participant discomfort is recorded in a serious adverse event form and simultaneously reported to the ethics committee and steering committee. These committees will determine if any further action is required, such as suspending data collection.

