PL refers to improved performance of a visual task with repeated practice or training [22, 23]. PL can enhance performance across a wide range of visual tasks including vernier acuity, contrast sensitivity, and motion direction discrimination [22, 24, 25]. The mechanisms underlying PL include altered tuning of neural populations and a gradual reweighting of inputs to perceptual decision-making networks [26]. The application of PL to glaucoma patients is still at an early stage, although initial clinical trial results have been reported. For example, Sabel and Gudlin [27] observed that 3 months of daily training (6 days per week for 1 h per day) significantly improved detection accuracy and reaction time measured using high-resolution perimetry (HRP) compared to a placebo. However, the absence of interim assessments throughout the long duration of intensive training has obscured the dose-response relationship. The confirmation of a dose-response relationship would provide stronger evidence supporting the practical application of PL in glaucoma rehabilitation.

tES is a non-invasive brain stimulation technique that can modify the excitability and synchronization of targeted neural regions and networks. The stimulation is achieved by delivering a mild electric current through electrodes mounted on the head that alters ongoing brain activity [28]. There is a growing body of evidence suggesting that tES could be a useful tool for vision rehabilitation [29, 30]. For example, tES has been found to improve vision in a wide range of clinical conditions, including age-related macular degeneration [31, 32], retinitis pigmentosa [33], amblyopia [20, 34], and hemianopia [35, 36]. Furthermore, results from our phase 1 study in the GREAT (Glaucoma Rehabilitation using ElectricAI Transcranial stimulation—NCT04846140) revealed that a single session of anodal transcranial direct current stimulation (tDCS) enhanced perceptual and electrophysiological measures of vision in patients with glaucoma [37]. Besides, tES is a non-invasive technique that is generally safe and typically associated with only mild, transient discomfort [38, 39]. Therefore, the potential application of tES as a tool for vision rehabilitation in glaucoma patients is promising.

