Participants will be randomly assigned to three different groups.Real PL + real tES. In this group, participants will receive 30 training sessions (10-time training × 3 blocks) with real PL and real tES (2 ~ 3 sessions per week, about 1 h per session).Real PL + sham tES. In this group, participants will receive 30 training sessions (10-time training × 3 blocks) with real PL and sham tES (2 ~ 3 sessions per week, about 1 h per session).Placebo PL + sham tES. In this group, participants will receive 30 training sessions (10-time training × 3 blocks) with placebo PL and sham tES (2 ~ 3 sessions per week, about 1 h per session).

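### The harms rule puts any discomfort on a serious adverse event form, although the protocol expects mild discomfort from tES, so SAE counts from these forms would be inflated

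*Protocol article*

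**What the plan says.** The section on adverse event reporting and harms {22} casts a wide net: "Participants are closely monitored for any discomfort throughout the interventions and assessments". It then fixes how what is found is recorded and reported: "Any participant discomfort is recorded in a serious adverse event form and simultaneously reported to the ethics committee and steering committee". The next step is a decision by those bodies: "These committees will determine if any further action is required, such as suspending data collection". The section names no other form and gives no criterion for what makes an event serious.

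The background and rationale {6a} sets the expectation for the stimulation: "tES is a non-invasive technique that is generally safe and typically associated with only mild, transient discomfort".

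On independent safety review, the data monitoring committee section {21a} reads "Not applicable. The intervention is non-invasive and has been proven safe". The ethics and steering committees are therefore the only bodies named as receiving these forms.

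**The concern.** An SAE label carries a specific meaning: the event met a seriousness criterion. The harms section attaches the SAE form to something far wider, any discomfort at all, in a trial that expects mild and passing discomfort from one of its own interventions. The recording rule and the stated expectation do not fit together.

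Two things are at stake, neither of them the primary efficacy result.

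- **Reporting of harms.** If SAEs are counted from these forms, the count mixes a brief skin sensation with an event that really was serious. A reader could not tell how many of the second kind occurred.
- **Oversight during the trial.** The committees may decide on steps as weighty as suspending data collection. Under the rule, what reaches them is a stream of forms under one label, not sorted by seriousness. With no data monitoring committee, no independent body is named that would do the sorting.

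**Working it through.** The article gives no adverse event rate and no SAE count, so there is no figure to reproduce. The check is mainly a comparison of the text, followed by an illustration of scale.

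**Step 1: what triggers the form.** In {22} the trigger is any discomfort in any participant. Monitoring covers assessments as well as interventions, so discomfort on the moving balance platform takes the same route as a sensation under the electrodes. No qualifier of severity, seriousness or relatedness appears.

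**Step 2: what is expected.** In {6a}, mild and transient discomfort is the kind of effect associated with tES. The sentence describes how mild the effect is and gives no frequency.

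**Step 3: put together.** An effect that {6a} calls mild and transient meets the trigger in {22}. It therefore goes on a serious adverse event form and to two committees at once. This follows from the stated rule. It does not depend on anything left out of the article.

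**Step 4: scale, under an assumed rate.** Inputs from the documents:

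- Participants: 144 (Sample size {14}: "a sample of 144 glaucoma patients will be needed to provide 80% power"), a figure that already allows for 20% dropout.
- Sessions per participant: 30 in each arm (Intervention description {11a}; for the combined arm, "participants will receive 30 training sessions (10-time training × 3 blocks) with real PL and real tES").
- Allocation: 1:1:1, so about 144 / 3 = 48 per arm, with real tES in one arm only.

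Sessions at full attendance: 144 × 30 = 4,320 in total; 48 × 30 = 1,440 per arm.

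Sessions if the 20% who drop out attended none (a lower extreme): 144 × 0.80 × 30 = 3,456.

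Forms = sessions × share of sessions with some discomfort. The share is an assumption; the documents give none.

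| Assumed share | One arm, 1,440 sessions | All arms, 4,320 sessions | All arms, 3,456 sessions |
|---|---|---|---|
| 1% | 14 | 43 | 35 |
| 5% | 72 | 216 | 173 |
| 30% | 432 | 1,296 | 1,037 |

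The all-arm columns apply one rate to every arm, so they say nothing about imbalance between arms. They also leave out discomfort at assessment visits. They show only that even a low rate would yield dozens of serious-event forms, none of which need record a serious event.

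**The case against.** The strongest reply is that this is loose wording in a condensed article. Entering something on a form is not the same as classifying it. The form is not shown and may already carry severity and seriousness fields, and the full protocol may define seriousness. Over-reporting to committees is also a cautious way to run oversight.

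Part of this stands. The article does not say that every form is counted as an SAE, so inflation of the count is conditional on counts being taken from the forms. The absence of seriousness criteria would not by itself be a finding in an article. But the article does not stay silent here: it states a rule, and the rule ties any discomfort to the serious-event form. A fuller document that separated the two would contradict that sentence. Over-reporting may be cautious for alerting a committee, but it does not help in describing how many serious harms occurred.

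A reader might also infer stronger consequences, which the documents do not support:

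- **That SAE counts by arm will be wrong.** The article lists no adverse event outcome and describes no comparison of SAEs between arms, and {20b} says that no additional analyses will be conducted.
- **That the combined arm will show a spurious excess.** Only that arm receives real tES, so imbalance is possible. But the documents give no rates of sensation for real or sham stimulation, so neither its presence nor its size can be shown.
- **That true serious events will be buried.** Every form goes to both committees at once, and nothing in the text delays or filters a serious event. What can be supported is dilution and extra reporting load.
- **That the forms are the only safety information anyone sees.** The steering committee consists of core team members {5d}, researchers report challenges to the principal investigator weekly {23}, and investigators accompany participants. The forms are the only adverse event reporting route that the article states, which is a narrower claim.

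**Conclusion.** The point holds in a limited form. The harms rule, as written, does not separate expected non-serious events from serious ones and sits badly with the background section. An SAE count drawn from these forms would be inflated and hard to interpret, and the signal reaching the committees would be diluted.

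The size cannot be fixed from the documents. The range of about 43 to 1,296 forms rests on full attendance and an assumed 1% to 30% of sessions with discomfort, and the conclusion does not depend on it. Whether the arms would differ is unknown. The primary analysis of visual field mean deviation is not affected. The correction is worth making because it is cheap and because the trial's account of serious harms depends on it.

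**What to change.** Reword {22} so that it agrees with {6a}:

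1. Record all discomfort on an adverse event form with fields for severity, relatedness and seriousness (yes/no).
2. State standard seriousness criteria, and keep the SAE form and the SAE label for events that meet them.
3. Report adverse events and SAEs separately.
4. Reclassify any forms already filed against the same criteria, by someone without access to the allocation.

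This changes recording and labelling only. Which reports the committees receive at once, and what they do with them, is for the sponsor and the ethics committees to settle when the two sections are reconciled.

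The cost is one protocol paragraph, one form revision and a small blinded relabelling task. The timing allows it: recruitment is planned to run to December 2026 {15}, unblinding follows data lock {17b}, and the amendment procedure {25} already provides for updating study forms.
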